#### Data collection and management

After consent, enumerators conduct interviews with the person who identifies themselves to the enumerator as being knowledgeable about water acquisition and use in his or her household. In addition to the water insecurity experience items described above (Module Versions 1 or 2), data are collected on sociodemographic characteristics; water acquisition, use and storage; household food insecurity (using the Household Food Insecurity Access Scale^28^); perceived stress (using a modified, four-item perceived stress scale^43^); and data quality (online supplementary material 2). These additional data will be used to validate the scale and explore other water insecurity phenomena in a cross-cultural manner.^44^ Each interview lasts approximately 45 minutes, and we expect data collection to last approximately 10–14 days in each standalone survey site (table 3).

10.1136/bmjopen-2018-023558.supp2Supplementary file 2

Implementation of HWISE data collection began in March 2017 and is expected to end in late 2018. Data collection with Module Version 1 began in March 2017 and is ongoing (table 3, currently n=4817). Data collection using Module Version 2 began in November 2017 and is also ongoing (currently n=3310).

Data are collected using both paper and tablet-based collection platforms, that is, Open Data Kit (ODK), opendatakit.org^45^; CSPro, csprousers.org; and KOBOToolbox (Cambridge, Massachusetts, USA; kobotoolbox.org). To reduce data collection errors, tablet-based platforms are programmed to include permissible ranges of responses, skips for questions that are not applicable and survey items in the language(s) most common to each study site. Most responses from paper surveys are entered by enumerators, study coordinators, data managers and/or site primary investigators into an online data collection platform (Enketo; enketo.org). Microsoft Excel is used when reliable internet access is unavailable.

Data are uploaded to a secure centralised aggregate server (Google App Engine). Stata 14 is used for data cleaning following a data cleaning protocol agreed on by the HWISE RCN (online supplementary material 3).

10.1136/bmjopen-2018-023558.supp3Supplementary file 3

#### Implementation fidelity

To ensure implementation fidelity, enumerators are debriefed daily following data collection. Both enumerators and site PIs are debriefed postimplementation (online supplementary material 4). Furthermore, each survey contains a module on perceived data quality (eg, explanation of missing data, distractions and issues with recruitment) that is filled in by the enumerator immediately postinterview.

10.1136/bmjopen-2018-023558.supp4Supplementary file 4

#### Analytic strategy

Three software packages will be used for analyses: Stata 14 to run basic descriptive statistics; Mplus version 8 (Muthén & Muthén, Los Angeles, California, USA) and Stata 14 for classical test theory analysis; and WINSTEPS (Winsteps, Beaverton, Oregon, USA) for item response theory (Rasch) analysis.

Scale development (table 1, 2.1–2.4) and evaluation (table 1, 3.1–3.3) will be informed by analyses corresponding to two scaling theories: classical test theory,^46^ implemented by factor analysis, and item response theory,^47^ using Rasch models.

### Item reduction

First, items with large cumulative missing cases (>30%), that is, ‘don’t know’, ‘non-applicable’ or true missing responses, will be dropped (table 1, 2.2). This will help to eliminate items that are not understood or are not widely applicable, and therefore do not reflect cross-cultural experiences of water insecurity.

Thereafter, items will be further dropped based on low correlation coefficients. In classical test theory, we will identify items with low (<0.30) interitem and item-total correlation coefficients across the multiple sites in this study.^10 48^

Within the Rasch paradigm, we will identify and remove items that misfit the models by assessing infit and outfit.^49 50^ Conditional item independence (ie, items conditional on the scale that are not correlated) will be assessed using residual correlation metrics. Items will be dropped if residual correlation is >0.20.^51^

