## Methods and analysis

### Phase 1: item development

#### Domain specification

Specifying the domains for a scale is the first step in item development (table 1, 1.1).^33 34^ The boundary of the domain of water insecurity, that is, the underlying construct that the scale will attempt to measure, was based on extensive literature review^1^ and draws on the team’s expertise in water insecurity, for example.^4 8 23 35^ We define water insecurity as the condition where ‘affordability, reliability, adequacy, and safety [of water] is significantly reduced or unattainable so as to threaten or jeopardize well-being’.^1^

**Table 1 T1:** Overview of planned methods and analyses for the development of the HWISE Scale*

Scale development activity	Procedures
Phase 1: item development	
1.1 Domain specification	Literature review.
1.2 Item generation	Literature review and Delphi methodology.
1.3 Content validity	By target population: two styles of cognitive interviews were used in the first eight sites, building on Delphi methodology.
1.4 Face validity	Pretesting and debriefing with enumerators at each site.
Phase 2: scale development	
2.1 Data collection	Enumerator training and survey implementation.
2.2 Item reduction	We will drop items with cumulative missing cases >30% (ie, ‘don’t know’, ‘non-applicable’ or true missing responses) in any one site.
	We will assess the performance of each item’s variation with other items in the scale using a correlation matrix; items with very low (<0.30) interitem correlation coefficients and very low (<0.30) item-total correlation coefficients across multiple sites will be considered for deletion, as will items that misfit the model, that is, with residual correlations >0.20.
	Item reduction in Rasch paradigm: item severity and item discrimination test.
2.3 Identify factor structure	We will use factor analysis across multiple sites to test for factor structure; items with very low factor loadings (<0.30), split factor loadings (high factor loadings (>0.50) in two domains) and high residual variances will be considered for deletion.
2.4 Assess measurement equivalence	We will use multigroup confirmatory analysis (a form of measurement invariance) on data from multiple sites to test for exact invariance in the hypothetical scale; invariance will be assessed in terms of factor structure (configural model), factor loadings (matric model), mean intercepts (scalar model) and factor means (strict model).

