	We will use confirmatory factor analysis alignment optimisation to estimate the group-specific factor means and variances of scale items across all sites; it assesses approximate invariance of scale items across multiple sites.
Phase 3: scale evaluation	
3.1 Score scale items	Finalised scale items will be used in their unweighted form as sum scores or in weighted form as factor scores.
3.2 Assess reliability (internal consistency) of scale items	We will use Cronbach’s alpha and the Rasch reliability statistic to test the internal consistency of the scale items within each site and aggregated across sites.
3.3 Assess scale validity	We will measure predictive, convergent and discriminant validity of the final scale items using criteria that were selected based on their strong theoretical relevance in the water insecurity literature; tests of water insecurity differences between ‘known groups’ will also be performed.

*Adapted from ref 34.

A best practice is to clearly articulate subdomains of the eventual scale, if they are known.^34 36^ Although some subdomains of water insecurity have been proposed,^1 5 11 37^ there is currently no consensus in the literature. Therefore, we will assess subdomains during the analytic phase.

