#### Item generation

Candidate scale items were identified deductively, based on an extensive literature review of items used in prior site-specific household water insecurity scales^1^ (table 1, 1.2). This includes team members’ prior work in *colonias* in the USA-Mexico boderlands^23^; a squatter settlement in Cochabamba, Bolivia^4^; in rural, periurban and urban households in Kenya^10^; and elsewhere, including rural areas in Ethiopia^5^ and Uganda.^24^ Initial items include experiences of water insecurity that have consequences for psychosocial and physical health, nutrition, impacts on livelihoods and household economy, and agriculture (online supplementary file 1).

10.1136/bmjopen-2018-023558.supp1Supplementary file 1

Each question is phrased to elicit experiences within the prior 4 weeks or month (ie, ‘In the last four weeks, how frequently have…’). This recall period was systematically determined using the Delphi method of consensus building with international and local experts in water insecurity, food insecurity and scale development and by comparing the responses in this recall period to a prospective daily recall of water insecurity experiences.^10^ Items were ordered by what we expected to be increasing severity of water insecurity across access, reliability, adequacy and safety. Response options are ‘never’ (0 times), ‘rarely’ (1–2 times), ‘sometimes’ (3–10 times), ‘often’ (11–20 times), ‘always’ (more than 20 times), ‘not applicable’, ‘don’t know’ or refused. Response intervals were also determined using the Delphi method.^10^

The initial set of 32 items is referred to as ‘Module Version 1’. This set of items was modified slightly in August 2017 (see ‘Mid-study Evaluations’ under Phase 3) based on feedback received from consortium members, survey implementers and other water security experts during a 3-day conference at Northwestern University. Modifications included slight rephrasing of 18 items to improve comprehension by participants and to elicit experiences related to water overabundance, two questions were added in an effort to capture cultural components of water and six items were eliminated for being too rare or idiosyncratic. The resultant set of 28 items is referred to as ‘Module Version 2’ (online supplementary file 1).

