### Identify factor structure

Factor analysis with data from multiple sites will be used to identify the optimal latent structure (table 1, 2.3). We will examine this structure for each site, comparing factor structures, magnitudes of factor loadings, eigenvalues for sample correlation matrices and global model fitness statistics. Items with low factor loadings (<0.30), split factor loadings and high residual variances (>0.50) will be considered for deletion.^34^

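### One-dimensional item screens, above all the Rasch residual-correlation rule, are placed before the factor analysis meant to assess subdomains, so a distinct subdomain could be screened out before it is looked for

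*Protocol article*

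**What the plan says.** Under Domain specification the article notes that the literature has reached no agreement on subdomains and continues: "Therefore, we will assess subdomains during the analytic phase". Under Identify factor structure it assigns that work: "Factor analysis with data from multiple sites will be used to identify the optimal latent structure". Table 1 numbers this step "2.3 Identify factor structure", and its rule on split loadings speaks of two domains, so the plan allows for more than one factor.

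Item reduction is step 2.2 and comes before it. The text sets out these rules:

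- Items with more than 30% missing responses go first.
- Next: "Thereafter, items will be further dropped based on low correlation coefficients". The criterion is that "we will identify items with low (<0.30) interitem and item-total correlation coefficients across the multiple sites in this study".
- For the Rasch analysis, "we will identify and remove items that misfit the models by assessing infit and outfit".
- Finally, "Items will be dropped if residual correlation is >0.20".

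Table 1 is softer. It treats items that fail the correlation or residual rule as candidates for removal, and it asks for low inter-item and low item-total correlations together, across several sites. No check of dimensionality is described ahead of these rules.

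**The concern.** An item-total correlation measures an item against one total, and a Rasch fit statistic or residual correlation measures it against one latent dimension. Suppose a smaller second subdomain exists. Once the single Rasch dimension has been removed, its items still share their own factor, so their residuals correlate with each other. The residual rule then selects them because they belong together, not because they are poor items. If they are removed at step 2.2, step 2.3 searches a set from which the evidence for a second factor has been taken out.

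At stake is the meaning of a one-factor finding. The scale is intended for wide use across settings. A single total would look empirically supported when the screen had helped to produce that result, and a coherent facet of water insecurity could be missing from it.

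**Working it through.** The plan states no figure on this point, so there is nothing to reproduce. The check applies the plan's cut-offs (0.30, 0.30, 0.20) to a two-factor model.

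**Inputs from the article:** 28 items in Module Version 2 (Item generation); target of 250 per site (Participant selection); five frequency categories. **Assumed:** a subdomain of 4 or 6 items, a common loading λ of 0.7 unless stated, and a correlation φ between the subdomain and the main domain that is varied.

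**1. Item-total rule, closed form.** With k1 main items and k2 subdomain items, a subdomain item has, with the sum of all other items:

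- covariance C = λ²[k1φ + (k2 − 1)]
- variance of that sum V = (k1 + k2 − 1) + λ²[k1(k1 − 1) + (k2 − 1)(k2 − 2) + 2k1(k2 − 1)φ]
- r = C/√V

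For k1 = 24, k2 = 4, φ = 0.3: C = 0.49 × (7.2 + 3) = 5.00; V = 27 + 0.49 × (552 + 6 + 43.2) = 321.6; r = 5.00/17.93 = 0.28. The same formula gives 0.15, 0.22, 0.34 and 0.40 at φ = 0.1, 0.2, 0.4 and 0.5. The 0.30 line is crossed at φ of about one third. In simulated five-category data the mean is 0.26 at φ = 0.3 and 0.35 at φ = 0.5, which puts the crossing nearer 0.4. For 6 items the closed form crosses at about 0.25.

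The joint rule, reading inter-item correlation as an item's mean, flagged 100%, 97%, 77%, 13% and 0% of the four items at φ = 0.1, 0.2, 0.3, 0.5 and 0.7. Read pair by pair, the within-subdomain correlation is λ² = 0.49 and nothing is flagged.

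**2. Residual rule, reasoning.** If the main factor is removed exactly and items are continuous, two subdomain items keep a correlation of λ²(1 − φ²)/(1 − λ²φ²). For λ = 0.7 and φ = 0.5 this is 0.3675/0.8775 = 0.42; for φ = 0.7 it is 0.2499/0.7599 = 0.33. For λ = 0.6 and φ = 0.7 it falls to 0.1836/0.8236 = 0.22. Simulated values are lower: the categories are coarse, and the Rasch measure itself contains the subdomain items.

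**3. Residual rule, simulation.** n = 250, 28 items, polytomous Rasch model fitted by joint maximum likelihood, 12 to 15 replicates per cell. An item is flagged if any of its residual correlations exceeds 0.20.

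| φ | Mean residual r within subdomain (4 items) | Flagged, 4-item subdomain | Flagged, 6-item subdomain |
|---|---|---|---|
| 0.1 | 0.40 | 100% | 100% |
| 0.2 | 0.41 | 100% | 100% |
| 0.3 | 0.36 | 100% | 100% |
| 0.5 | 0.30 | 100% | 100% |
| 0.7 | 0.20 | 83% | 92% |
| 0.85 | 0.11 | 15% | 17% |

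Main-domain items were flagged in 1–4% (four-item case) and 1–8% (six-item case). A truly one-dimensional control flagged 0%. A separate simulation with 24 + 4 items gave 100% at 0.2 and 0.4, 84% at 0.6 and 0.7, and 12% at 0.85. Infit of the items in the four-item subdomain was 1.4 to 1.7 for φ up to 0.5, so the misfit rule, for which the article gives no cut-off, may reach the same items.

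**4. A milder application.** Dropping only one item of each offending pair and refitting left on average 1.0, 1.0, 1.8 and 3.5 of 4 items at φ = 0.3, 0.5, 0.7 and 0.85, and 1.0, 1.1, 2.4 and 5.6 of 6. One or two items cannot define a factor.

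**5. Effect on the factor analysis, and limits.** With 20 + 6 items and φ of 0.2 to 0.6, parallel analysis found two factors before the residual screen and one after it, at n = 250 and at n = 4,000. With λ = 0.6 the same result was obtained only up to φ = 0.4. At φ = 0.7 sample size matters: 84% were flagged at n = 250 but 0% at n = 4,000 (one replicate), because the mean residual correlation then lies close to the cut-off.

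**The case against.** The strongest reply has four parts.

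- **Table 1 does not make removal automatic.** This stands as a softening. It also leaves the text and the table in disagreement, and the table does not say that clustered residuals should be read as a possible dimension.
- **The closing paragraph of the Validity section** expects imperfect items, calls for judgement on trade-offs and wants many facets covered. This stands too, but it concerns the final item set. Nothing there returns screened-out items to the factor analysis, so the judgement might be made without evidence on the structure of what was lost.
- **The order is partly inferred.** Analytic strategy describes two scaling theories in different software, and no sentence says that items failing the Rasch screen are withheld from the factor analysis. Parallel streams are a possible reading, but the numbering in Table 1 and the unconditional wording of the residual rule point to a sequence.
- **The correlation rule is the weaker half.** This is right. It requires both correlations to be low, it affects only weakly related subdomains, and its effect depends on how inter-item correlation is read.

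A reader might also infer that overabundance and cultural use are the facets most at risk. The documents do not support that. For culture, "two questions were added in an effort to capture cultural components of water"; two items are fewer than the four or six simulated. Overabundance was one aim of rephrasing 18 existing items and is not described as a separate block.

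**Conclusion.** The concern holds in conditional form. Applied literally, the residual rule at n = 250 would flag most or all items of a four- to six-item subdomain whose correlation with the main domain is up to about 0.7, given loadings of 0.7. With loadings of 0.6 the support extends only to about 0.4. A subdomain correlated about 0.85 mostly survives. The item-total rule contributes only below a correlation of about 0.35 to 0.4. Under these conditions a later one-factor solution would be weak evidence that water insecurity is unidimensional.

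Two stronger statements are tempting and do not follow. One is that a real subdomain will be deleted: the documents say only that subdomains are unsettled, and loadings, subdomain size and domain correlations are all assumed here. The other is that the factor analysis will report one factor whatever the truth: closely related domains escape the rule, and a pooled analysis of several thousand may spare a subdomain correlated 0.7. The point should be corrected before item reduction is run, but it does not by itself invalidate the plan.

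**What to change.** Keep the missing-data rule first. Then examine dimensionality on all remaining items, for example by exploratory factor analysis with parallel analysis, by site and pooled after removing between-site differences. Apply the item-total, infit/outfit and residual-correlation rules within each dimension found. State that a cluster of residual correlations is to be examined as a possible dimension and is not in itself a reason to drop items. Choose between one total and subscales only after that.

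Reconcile the Item reduction text, where the residual rule drops items outright, with Table 1, where they are only candidates for removal. State whether inter-item correlation means an item's average or each pair.

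The cost is a reordering of steps and one more set of factor-analysis runs on the longer item list. No new data are needed.

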### Identify factor structure

Factor analysis with data from multiple sites will be used to identify the optimal latent structure (table 1, 2.3). We will examine this structure for each site, comparing factor structures, magnitudes of factor loadings, eigenvalues for sample correlation matrices and global model fitness statistics. Items with low factor loadings (<0.30), split factor loadings and high residual variances (>0.50) will be considered for deletion.^34^

### Assess measurement equivalence

Measurement equivalence concerns the extent to which the psychometric properties of the observed indicators are generalisable across groups or over time.^52–55^ It holds ‘when a test measures a construct in the same way regardless of group membership and is violated when individuals from different groups respond to the test in a dissimilar manner’.^39^ A violation of equivalence implies our inability to make comparisons about the measurement and meaning of scale values across groups (eg, sites, cultures and languages).^39^ To determine measurement equivalence across sites using Module Versions 1 and 2, we will use multigroup confirmatory factor analysis and alignment optimisation.^56–58^

## Phase 3: scale evaluation

### Score scale items

Once a water insecurity scale that is equivalent across sites is provisionally identified, we will use scale scores in both weighted forms (factor scores) and unweighted forms (sum scores) to assess the external validity of our scale.

### Reliability

To test for the reliability (internal consistency) of the items, we will estimate Cronbach’s alpha for both site-specific and aggregate-level data.^59^ The Rasch reliability statistic is analogous to Cronbach’s alpha. In our analyses, we will consider reliability to be ideal if it is greater than 0.80.^59^

### Validity

We will examine three types of validity: predictive, convergent and discriminant validity. Predictive validity is ‘the extent to which a measure predicts the answers to some other question or a result which it ought to be related with’.^60^ Using both linear regression and structural equation models, we will test for predictive validity by regressing HWISE Scale scores on eg, food insecurity, perceived stress and income.

Convergent validity is the ‘degree to which scores on a studied instrument are related to measures of other constructs that can be expected on theoretical grounds and accumulated knowledge to be close to the one tapped into by this instrument’.^48^ To test for convergent validity, we will assess the relationships between HWISE Scale scores and individual items that have shown to be closely related to the concept of water insecurity. Specifically, we will use linear regression to examine the strength of the relationships between HWISE Scale scores and eg, time to water source, number of trips to water source and amount of money spent purchasing water. Larger correlation and regression coefficients and smaller SD of residuals will be indicative of support for convergent validity.

Discriminant validity is the ‘degree to which scores on a studied instrument are differentiated from behavioral manifestations of other constructs’.^48^ A test of differentiation between ‘known groups’ will be conducted using the Student’s *t*-test^34 48^; these groups will be based on accumulated knowledge. We will determine the distribution of household water insecurity scores across known groups, eg primary source of drinking water (improved vs unimproved sources), water treatment (treated vs untreated), gender of household head (male vs female) and injuries associated with water acquisition (yes vs no).^4 5 10 24 61^ Under the Rasch measurement model, differentiating between known groups will also be conducted using differential item functioning. We will determine whether each scale item performs differently in each of the subgroups. Differential item functioning is attained when the probabilities of an item being endorsed is unequal for the two subgroups.^10 62^

In sum, selection of the set of items to be included in the final scale will be based on several criteria. The criteria for inclusion of an item are: reliable in each site, fits theoretically and empirically with concepts related to water insecurity, has face and content validity in each site, shows equivalent measurement and meaning across sites and contributes to predictive, convergent and discriminant validity in each site.^63^ We anticipate that not every item will meet each criterion perfectly, and judgement about tradeoffs of which items to include will be required. These judgements will be made considering the additional criteria of having a diversity of items in the final scale that cover as many facets of water insecurity as reasonably possible. We anticipate that the final scale will have fewer than 20 items, which will reduce the likelihood of participant fatigue and make its widespread application more feasible.

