**Methods and analysis:**

After domain specification and item development, items were assessed for both content and face validity. Retained items are being asked in surveys in 28 sites globally in which water-related problems have been reported (eg, shortages, excess water and issues with quality), with a target of at least 250 participants from each site. Scale development will draw on analytic methods from both classical test and item response theories and include item reduction and factor structure identification. Scale evaluation will entail assessments of reliability, and predictive, convergent, and discriminant validity, as well as the assessment of differentiation between known groups.

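### The procedures described under discriminant validity are known-groups tests that cannot show whether HWISE is distinct from other constructs; as a lesser point, the predictive regression is worded with HWISE as the outcome

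*Protocol article*

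**What the plan says.** The Validity section (Phase 3) opens with "We will examine three types of validity: predictive, convergent and discriminant validity". Each type is then defined and given a procedure.

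- **Predictive validity** is "the extent to which a measure predicts the answers to some other question or a result which it ought to be related with". The procedure is introduced with "Using both linear regression and structural equation models" and continues: "we will test for predictive validity by regressing HWISE Scale scores on eg, food insecurity, perceived stress and income".
- **Discriminant validity** is the degree to which "scores on a studied instrument are differentiated from behavioral manifestations of other constructs". The next sentence moves to a test between known groups, which "will be conducted using the Student’s" t-test. The example groups are drinking-water source, water treatment, gender of household head and injuries from fetching water. Differential item functioning is then given as the Rasch version of the same known-groups comparison.

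Elsewhere the article keeps the two ideas apart. The Abstract names discriminant validity among the validity assessments and then adds "as well as the assessment of differentiation between known groups". Table 1, row 3.3, likewise presents known-groups tests as additional. The paragraph closing the Validity section makes an item's contribution to discriminant validity, site by site, one of the criteria for keeping it. Data collection and management lists "household food insecurity (using the Household Food Insecurity Access Scale") and a modified four-item perceived stress scale among the data collected at interview.

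**The concern.** Discriminant validity asks whether a scale measures something different from neighbouring constructs. A known-groups comparison asks whether the scale separates people who should differ on the construct itself. A scale can do the second well and still be hard to tell apart from a neighbour.

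The question matters for this scale. The Introduction says that water and food insecurity have been shown to co-occur. Item generation says that the initial items include water experiences with consequences for psychosocial health and nutrition. If the plan is followed as written, a claim of discriminant validity, and item choices that depend on it, would rest on a test that does not address overlap.

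The predictive wording raises a smaller issue. The definition makes the scale the predictor, while the model sentence makes it the dependent variable.

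**Working it through.** The plan states no figure for these tests, so there is nothing to reproduce. The check compares each definition with its procedure.

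**1. Definition against procedure**

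| Type | Definition requires | Procedure described | Match |
|---|---|---|---|
| Predictive | HWISE predicts another result | HWISE regressed on food insecurity, stress and income | Direction reversed |
| Convergent | HWISE is related to close measures | Linear regression relating HWISE to time to source, number of trips and money spent on water | Yes |
| Discriminant | HWISE is separated from other constructs | HWISE t-test across known groups; differential item functioning across subgroups | No other construct enters |

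**2. What the t-test can respond to.** For two groups,

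t = (mean HWISE in group 1 − mean HWISE in group 2) / standard error.

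Every term is a function of HWISE scores and group labels. No food insecurity or stress score appears, so for given HWISE scores t is the same whatever their correlation with another construct.

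A simulation illustrates this. The assumptions, none of them from the plan, are 125 per group (half the 250 target), a 0.5 SD difference in HWISE and 3,000 runs per setting.

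| Correlation of HWISE with the other construct | t-test significant at 5% |
|---|---|
| 0 | 97.5% |
| 0.5 | 97.8% |
| 0.95 | 97.6% |

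The power formula gives 97.7%. The simulation standard error is √(0.977 × 0.023 / 3000) ≈ 0.3 percentage points, so the three results do not differ beyond noise.

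Differential item functioning has the same limit. It asks whether an item behaves differently in two subgroups, and no other construct is measured in it.

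**3. What the reversed regression changes.** With one predictor,

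t = r√(n − 2) / √(1 − r²), and R² = r².

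Both are symmetric in the two variables. Take n = 250 and an assumed r = 0.4 between HWISE and food insecurity:

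- t = 0.4 × √248 / √0.84 = 6.87 in either direction
- R² = 0.16 in either direction

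The slope is r × SD(outcome) / SD(predictor). With assumed SDs of 10 for HWISE and 5 for food insecurity:

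- HWISE on food insecurity: 0.4 × 10/5 = 0.80
- Food insecurity on HWISE: 0.4 × 5/10 = 0.20

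Direction therefore changes the slope, and it reverses the path in a structural equation model. It leaves the evidence of association alone.

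**4. If the criteria entered together.** The article does not say whether they do. Assumed correlations are HWISE–stress 0.3, HWISE–income −0.2, food–stress 0.4, food–income −0.3 and stress–income −0.2, with n = 250.

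| Assumed HWISE–food r | t for food insecurity alone | t with stress and income also in the model |
|---|---|---|
| 0.2 | 3.21 | 0.90 |
| 0.4 | 6.87 | 4.86 |
| 0.6 | 11.81 | 9.92 |

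This change comes from adjusting for the other criteria, not from direction. The partial t is also symmetric: food insecurity regressed on HWISE, stress and income would give the same value for HWISE.

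**The case against.** Several points can be made for the plan.

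- **The plan knows the difference.** The Abstract and Table 1 separate known groups from discriminant validity, so a reader should not infer that the authors treat them as one idea throughout. This stands. It also sharpens the point: discriminant validity is promised separately, and only a known-groups procedure is described under it.
- **The t-tests can fail.** A reader might infer that the claim would rest on tests bound to succeed. The text does not support that, since a contrast such as gender of household head may well be null. The narrower statement holds: a null or positive result says nothing about overlap with another construct.
- **Overlap would be visible anyway.** The predictive regressions and structural equation models relate HWISE to food insecurity and stress, so a very high correlation would show. This stands in part. No criterion says when an association is too strong for the constructs to be distinct, and under predictive validity an association is the hoped-for result.
- **A condensed article leaves detail to a fuller plan.** That covers a missing cut-off or model specification. It does not cover this, because the article does give a method under its definition, and the method addresses another property.
- **Regressing on may be loose wording.** It may be. A reader might also infer that the reversal distorts the tests of predictive validity. For single-criterion linear models it does not. The tests change materially only under joint entry, which the document does not specify.

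**Conclusion.** The discriminant point holds on the text alone and needs correcting before the validity claim is made or used to select items. As described, the procedures cannot detect a lack of distinctness between HWISE and food insecurity, stress or any other construct. This conclusion rests on no assumed effect size; the simulation only illustrates it.

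The predictive point also holds, with less weight. The model sentence contradicts the definition beside it. The effect is limited to slopes and the direction of structural paths if each criterion is modelled alone; t and R² are unchanged. The document does not support a claim that predictive validity would be wrongly accepted or rejected because of the reversal.

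The convergent procedure matches its definition and is not in question.

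**What to change.** **Discriminant validity**

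- Report the t-test and its groups under a separate known-groups heading, as the Abstract and Table 1 already imply.
- Name the comparison constructs and test distinctness with the Household Food Insecurity Access Scale and four-item stress data. One way is a joint confirmatory factor analysis with HWISE, food insecurity and stress as separate factors, reporting each latent correlation with its 95% confidence interval against a bound fixed in advance. A bound of 0.85 is one option. It does not come from the document and is for the sponsor to choose.

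**Predictive validity**

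- Reword so that each criterion is the dependent variable and HWISE the predictor, with one model per criterion and structural paths in the same direction. Income can stay on the list of criteria; the correction does not require changing its role.

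**Cost.** The change needs revised wording and one added analysis on data already being collected, in software already planned (Mplus). The discriminant claim could then fail. Intervals will also be wide at small sites, such as Acatenango with 101 respondents, so the plan should say whether the bound applies by site or to pooled data.
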